### Data collection

Data collection occurs with treatment and control group participants at Baseline, 3-Month, and 6-Month timepoints, with a +/- 30 day window. Additionally, the treatment group is contacted at the 12-Month timepoint to obtain long-term follow-up information. Within the clinical setting, providers collect Hemoglobin A1c (HbA1c) levels and lipid profile according to the standard of care lab schedule for management of each participant. Outside of the clinical setting, questionnaire data and several clinical endpoints (height, weight, blood pressure, and waist/hip circumference) are obtained; all procedures are completed in-language by CHWs or trained study personnel. In addition to the above timepoints, questionnaire data is collected at each one-on-one visit pertaining to access and utilization of primary and specialty care, as well as barriers encountered in maintaining a healthy diet, engaging in physical activity, and managing stressors. Figure 3 demonstrates procedures for each study group and overall flow of study design.

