In addition to educational sessions, treatment group participants receive two one-on-one visits during the six month study period. Each visit provides study participants with the opportunity to discuss individualized care needs related to diabetic management with a CHW, as well as to discuss goal-setting around health behaviors using motivational interviewing techniques. CHWs also help to provide referrals to specialty care (e.g. podiatry and dentistry), as well as to social service or community-based resources for needs related to housing, food assistance, immigration, etc. Lastly, CHWs utilize phone follow-up between educational sessions and one-on-one visits to both encourage adherence to discussed care plans, as well as to improve study retention and data collection rates by minimizing study drop-out. All of the above interactions with study participants are documented in CHW progress notes and call logs to ensure fidelity to study protocol as well as to capture secondary study outcomes related to access to and utilization of care.

Individuals randomized to the control group receive a one-time, introductory educational session only. This session focuses on general concepts regarding diabetes management, and is the same introductory session received by the treatment group. Individuals randomized to the control group are instructed to seek medical care as usual from their regular physician. Previous literature has underscored the importance of providing meaningful incentives as a strategy to maximize retention in community-based studies [33]. Accordingly, participants are provided round-trip MetroCards® ($4.50 - $5 value) at each educational session and at each data collection timepoint. Additionally, treatment group participants are given a small incentive related to the session topic (e.g. bag of brown rice, pill box, pedometer, etc.) at each session, as well as a ticket towards a $100 raffle drawing to be completed at the end of the intervention period.

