### Study outcomes

Primary study outcomes include: (1) decreased levels of HbA1c, lipid profiles, and systolic and diastolic blood pressure and a greater proportion of individuals with controlled blood pressure; (2) greater access and utilization of healthcare; and (3) a positive impact of knowledge and practice of physical activity and healthful eating. Secondary outcomes include: (1) increased levels of perceived social support; (2) greater perceived benefits and lower perceived barriers; and (3) higher levels of self-efficacy.

Clinical measures included HbA1c, lipid profile (cholesterol, HDL, LDL, and triglycerides), systolic and diastolic blood pressure, height, and weight. BMI is calculated at each timepoint using current weight and height recorded at baseline. Waist-to-hip ratio is calculated using waist and hip circumference measurements obtained at each timepoint. Blood pressure is collected using previously validated methods for community-based settings, given that data collection frequently occurred outside of the hospital [34]. Three resting blood pressure measurements approximately 2–3 minutes apart are collected at each timepoint using an OMRON HEM 711-AC automatic blood pressure monitor with participants in a seated position. The average of the second and third blood pressure readings is recorded as the final value. HbA1c and lipid profile were measured through a laboratory blood test.

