#### ***Predisposing & reinforcing characteristics***

Information on predisposing characteristics of study participants is collected at baseline only, and include health access and insurance status, length of time in the US, acculturation, marital status, socioeconomic status, and personal and family history of T2DM. Measures were primarily drawn from the Behavioral Risk Factor Surveillance System (BRFSS) [35]. Information on reinforcing characteristics, including self-efficacy [36], social support and social capital [37], and religiosity are collected at each timepoint.

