**Socio-demographic (pre-disposing characteristics):**				
Sex, age, marital status, country of birth, years in U.S., education, household size, home language, English fluency	✓			
Employment Status	✓	✓	✓	✓
Health insurance	✓			
Barriers to healthcare	✓			

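### Access to and use of care is to be compared between arms, but the only post-baseline sources the article names for it arise from treatment-arm contacts, so recording may be unequal and favour the intervention

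*Protocol article*

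**What the plan says.** All references are to the Protocol article.

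- **Rank of the outcome.** Study outcomes lists "greater access and utilization of healthcare" among the primary outcomes. Objectives places access to primary and specialty care under the secondary aims, and CHW intervention also calls these outcomes secondary.
- **Timing.** The Abstract (Methods/Design) explains access and utilization as appointment keeping and use of specialty care. It says outcomes are measured at baseline, 3 and 6 months in both groups.
- **Named follow-up sources.** Data collection says that "questionnaire data is collected at each one-on-one visit pertaining to access and utilization of primary and specialty care". CHW intervention says the interactions it has just described are written up in progress notes and call logs, partly "to capture secondary study outcomes related to access to and utilization of care".
- **Who generates those sources.** Under CHW intervention, "treatment group participants receive two one-on-one visits during the six month study period". The referrals and between-session calls belong to the same arm. Controls receive a single introductory session.
- **Shared items.** Predisposing & reinforcing characteristics describes information "collected at baseline only, and include health access and insurance status". In Table 1, Health insurance and "Barriers to healthcare" each carry one tick, at baseline. No row is named for access or utilization at 3, 6 or 12 months.
- **Analysis.** Data analyses plans t-tests or chi-square tests for each aim, with intervention group as the main predictor in the models.

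**The concern.** A between-arm difference in recorded use of care can be read as an effect only if use is ascertained in the same way in both arms. Here the sources tied by name to this outcome come from contacts that are themselves the intervention. The CHWs who make the referrals also document what follows. If a control participant's podiatry visit goes unrecorded because nobody asked, while a treatment participant's visit enters a CHW note, the arms will differ even when true use is the same. The error has one direction, towards the intervention.

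The Discussion concedes ascertainment bias from the lack of blinding. It does not mention that the arms may also differ in where the data come from.

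**Working it through.** The plan gives no figure for this outcome, so the main check is to set the text side by side. The arithmetic after it is illustrative.

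**1. Follow-up sources named for access and utilization, up to 6 months**

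| Source | Treatment | Control |
|---|---|---|
| Questionnaire at one-on-one visits (Data collection) | 2 visits | none |
| CHW progress notes and call logs (CHW intervention) | ongoing | none described |
| Access, insurance and barriers items (Predisposing & reinforcing characteristics; Table 1) | baseline only | baseline only |
| General statement that outcomes are measured at 3 and 6 months (Abstract) | yes, instrument not named | yes, instrument not named |

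The Abstract promises common follow-up. The sections that name instruments do not show which one delivers it for this outcome in controls.

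**2. Three readings of these passages**

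- (a) Common items exist at 3 and 6 months, and only those enter the comparison. There is then no bias from unequal sources.
- (b) Common items exist, and the treatment-only sources are added. Ascertainment is unequal.
- (c) No common follow-up items exist. The contrast cannot be estimated.

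**3. Size under reading (b)**

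Completers per arm: 256 / 2 = 128, and 128 × 0.75 = 96, which matches Sample size calculations.

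Assumptions (not in the article): true use p is the same in both arms; each occasion independently captures a user with probability s; the treatment arm has k = 4 occasions (3 months, 6 months and two one-on-one visits) and controls have k = 2. Notes and logs are ignored.

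Recorded use = p × (1 − (1 − s)^k). For p = 0.5 and s = 0.5:

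- treatment: 0.5 × (1 − 0.5^4) = 0.469
- control: 0.5 × (1 − 0.5^2) = 0.375

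The last column is the chance that a two-sided 5% test of two proportions with 96 per arm favours treatment (normal approximation; nominal 2.5% in that tail).

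| p | s | Treatment | Control | Difference | Chance of a false finding for treatment |
|---|---|---|---|---|---|
| 0.3 | 0.5 | 0.281 | 0.225 | 0.056 | 14.3% |
| 0.3 | 0.7 | 0.298 | 0.273 | 0.025 | 5.7% |
| 0.3 | 0.9 | 0.300 | 0.297 | 0.003 | 2.8% |
| 0.5 | 0.5 | 0.469 | 0.375 | 0.094 | 25.9% |
| 0.5 | 0.7 | 0.496 | 0.455 | 0.041 | 8.2% |
| 0.5 | 0.9 | 0.500 | 0.495 | 0.005 | 2.9% |
| 0.7 | 0.5 | 0.656 | 0.525 | 0.131 | 45.6% |
| 0.7 | 0.7 | 0.694 | 0.637 | 0.057 | 13.1% |
| 0.7 | 0.9 | 0.700 | 0.693 | 0.007 | 3.2% |

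A blunter illustration, also assumed: true use of 40% in both arms, with overall capture of 90% in treatment and 60% in control. Recorded use is then 0.40 × 0.90 = 36% against 0.40 × 0.60 = 24%, a 12-point difference with no true effect.

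**The case against.** The strongest reply is that the article does claim common measurement. The Abstract names this outcome and then says outcomes are measured in both groups at 3 and 6 months. Data collection introduces the one-on-one questionnaires as supplementary to that schedule and never calls them the sole source. The baseline-only items are listed as predisposing characteristics, alongside marital status and time in the US, so they may be covariates and not the outcome. Table 1 lists domains, not items, and Diabetes management, ticked at every timepoint, could hold care-use questions. The table as read also disagrees with the text elsewhere: height is ticked at 12 months only, while BMI uses baseline height. Figure 3 is not available to this review. An article may leave item lists to the full protocol. The capture rates above are assumed, and no passage says outright that the extra treatment-arm reports enter the between-arm test.

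Most of this stands. A reader might infer that controls have no follow-up data on care use and that the comparison is impossible. The article does not support that, given the Abstract's statement and the supplementary role of the visit questionnaires. A reader might also take the outcome as settled primary; only Study outcomes ranks it so.

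The objection does not remove the stated purpose of the notes and logs. CHW intervention says they serve to capture access and utilization outcomes, and they arise from treatment-arm contacts. That is a stated data source, not an omitted detail, and nothing confines it to process reporting.

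**Conclusion.** The point holds in a limited form. The article plans a between-arm comparison of access and utilization, promises common timepoints in general terms, and names follow-up sources for this outcome that arise only from treatment-arm contacts. If those sources feed the outcome, as CHW intervention states, ascertainment is unequal and biased towards the intervention.

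The size cannot be fixed from the article. It is nil if only common items are analysed. If extra occasions are pooled, it ranges from negligible (about 3% false findings for treatment at 90% capture per occasion) to large (about 46% at 50% capture and 70% true use). The contrast is inestimable only if no control data are collected. These figures rest on equal true use, independent occasions and 96 completers per arm.

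The HbA1c comparison, on which the sample size is based, is not affected by this point. The disagreement over primary or secondary rank bears on how much weight the result would carry; the need for equal ascertainment is the same at either rank.

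**What to change.** 1. Reconcile the Abstract, CHW intervention, Data collection, Predisposing & reinforcing characteristics and Table 1. Place identical access and utilization items (appointments kept, specialty visits, barriers) in the 3- and 6-month questionnaires for both arms and tick them in Table 1. If such items already sit in an existing domain, say which. Alternatively, extract encounter records by the same procedure in both arms.
2. State that the between-arm analysis uses that common source only.
3. Use one-on-one questionnaires, CHW notes and call logs for fidelity and process reporting in the treatment arm only.
4. Settle whether the outcome is primary or secondary and use one label throughout.

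**Cost.** A few items on questionnaires already given to both arms, and a short amendment. The treatment arm will show fewer recorded events than with all sources pooled. The Discussion says recruitment began in February 2011 and runs in cohorts, so if items were not asked, cohorts already past 3 and 6 months would need identically extracted records, and their data may be incomplete. A common source removes unequal capture; it does not remove the effect of unblinded data collectors, which the article already lists as a limitation.

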**Figure 3 F3:**
[figure not shown]
Overall study design flowchart.

### Study outcomes

Primary study outcomes include: (1) decreased levels of HbA1c, lipid profiles, and systolic and diastolic blood pressure and a greater proportion of individuals with controlled blood pressure; (2) greater access and utilization of healthcare; and (3) a positive impact of knowledge and practice of physical activity and healthful eating. Secondary outcomes include: (1) increased levels of perceived social support; (2) greater perceived benefits and lower perceived barriers; and (3) higher levels of self-efficacy.

Clinical measures included HbA1c, lipid profile (cholesterol, HDL, LDL, and triglycerides), systolic and diastolic blood pressure, height, and weight. BMI is calculated at each timepoint using current weight and height recorded at baseline. Waist-to-hip ratio is calculated using waist and hip circumference measurements obtained at each timepoint. Blood pressure is collected using previously validated methods for community-based settings, given that data collection frequently occurred outside of the hospital [34]. Three resting blood pressure measurements approximately 2–3 minutes apart are collected at each timepoint using an OMRON HEM 711-AC automatic blood pressure monitor with participants in a seated position. The average of the second and third blood pressure readings is recorded as the final value. HbA1c and lipid profile were measured through a laboratory blood test.

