## Methods/Design

### Objectives

The primary aim of the current study is to assess the efficacy of a CHW intervention to improve management and control among Bangladeshis with T2DM in NYC. Secondary aims include examining the intervention’s effect on diabetes knowledge, self-management practices, health behaviors, and access to primary and specialty care services among study participants.

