### Sample size calculations

The size of the study population is based on the primary outcome measure of HbA1c and was estimated by using previous changes observed in a pilot study as well as in previous research [19,20]. Control group HbA1c estimates were based on hospital patients receiving usual care. An absolute difference of 0.5% in HbA1c between the groups (6.7 vs. 6.2) with a power of 0.8 and significance level of 0.05 may be detected with a total of 40 individuals in each group, and an absolute difference of 0.3% in HbA1c between the groups (6.7 vs. 6.4) with a power of 0.8 and significance level of 0.05 may be detected with a total of 120 individuals in each group. The sample size calculation was based on a medium effect size of the primary outcomes between the intervention and control group. Approximately 256 enrolled study participants were randomized each to the treatment and control groups. We anticipated that 75% of study participants would be followed to completion of the study at 6 months (n = 96 in each group).

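### Access, knowledge and behavior outcomes are primary in one section and secondary in others, and of all the outcomes listed as primary only HbA1c is sized

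*Protocol article*

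**What the plan says.** All references are to the Protocol article.

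- *Sample size calculations*: "The size of the study population is based on the primary outcome measure of HbA1c". The first scenario reads "An absolute difference of 0.5% in HbA1c between the groups (6.7 vs. 6.2) with a power of 0.8 and significance level of 0.05" and "may be detected with a total of 40 individuals in each group". The second is a difference of 0.3 with 120 per group at the same power and level. No other outcome has a target difference or a power figure. The same paragraph later speaks of a medium effect on the primary outcomes, in the plural.
- *Study outcomes*: "Primary study outcomes include: (1) decreased levels of HbA1c, lipid profiles, and systolic and diastolic blood pressure", followed by the proportion with controlled blood pressure, access to and utilization of care, and knowledge and practice of physical activity and diet. The lipid profile is spelled out as cholesterol, HDL, LDL and triglycerides. The secondary outcomes here are social support, perceived benefits and barriers, and self-efficacy.
- *Objectives*: the primary aim is diabetes management and control. The secondary aims cover the intervention's "effect on diabetes knowledge, self-management practices, health behaviors, and access to primary and specialty care services among study participants".
- *CHW intervention*: progress notes and call logs serve in part "to capture secondary study outcomes related to access to and utilization of care".
- *Data analyses*: each aim gets t-tests, chi-square or Mann–Whitney tests and logistic regression. The section does not rank the outcomes. The Abstract lists primary and secondary outcomes together without separating them.

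**The concern.** A reader cannot tell from the article which result decides whether the intervention worked. On the sizing section it is HbA1c. On the outcomes section it could also be a lipid fraction, a blood pressure measure, use of care, or a knowledge or behavior score. Two other sections demote the last three.

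The trial could therefore report a favorable primary result on an outcome with no power figures while HbA1c shows nothing, and cite its own outcomes section in support.

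The disputed outcomes are also among those most exposed to bias. The Discussion accepts that staff and participants are unblinded and that ascertainment bias may follow. Data collection has questionnaires completed by CHWs or trained study personnel. The knowledge measures include what was learned at each educational session, while controls attend only the introductory one.

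**Working it through.** **1. The classifications side by side**

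| Outcome | Sample size calculations | Study outcomes | Objectives | CHW intervention |
|---|---|---|---|---|
| HbA1c | primary, sized | primary | not named (primary aim is diabetes control) | – |
| Lipids, blood pressure, controlled blood pressure | not sized | primary | not named | – |
| Access and utilization | not sized | primary | secondary (access) | secondary |
| Knowledge, behavior | not sized | primary | secondary | – |

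The last two rows contradict each other across sections. The second row is a mismatch between what is labelled primary and what is sized.

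**2. The plan's own sample-size figures**

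No SD is given, so 40 and 120 per group cannot be reproduced directly. For a two-sided 0.05 test (sidedness is also not stated) with 80% power, n = 2·SD²·(1.960 + 0.842)²/d². Solving for the SD:

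- d = 0.5, n = 40: SD = 0.5·√20 / 2.802 = 0.798
- d = 0.3, n = 120: SD = 0.3·√60 / 2.802 = 0.829

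A single SD of 0.817 gives 42 and 117, close to both stated figures, so they are not shown to be wrong. With 256 as the total, 256 × 0.75 / 2 = 96 per group, as stated. All of this concerns HbA1c only.

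**3. Count of endpoints labelled primary**

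1 HbA1c + 4 lipid components + systolic + diastolic + controlled blood pressure = 8. One test for each of the other two domains makes 10.

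**4. Chance of at least one false positive**

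Assumptions: no true effect, each endpoint tested two-sided at 0.05, no adjustment.

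- 8 independent tests: 1 − 0.95⁸ = 0.337
- 10 independent tests: 1 − 0.95¹⁰ = 0.401
- Favorable direction only, 8 independent tests: 1 − 0.975⁸ = 0.183

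For correlated endpoints, equicorrelated normal statistics were simulated (400,000 draws, 8 endpoints):

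| Common correlation | Either direction | Favorable direction only |
|---|---|---|
| 0 | 33.7% | 18.3% |
| 0.3 | 30.0% | 15.2% |
| 0.5 | 25.0% | 12.6% |
| 0.8 | 15.7% | 7.8% |
| Single test | 5% | 2.5% |

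**5. What keeping all eight as primary would cost**

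Bonferroni gives 0.05/8 = 0.00625 per endpoint. Power for HbA1c is Φ(d / (SD·√(2/n)) − z), with n = 96 per group and the back-solved SD range of 0.80 to 0.83:

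| Difference | At 0.05 | At 0.00625 |
|---|---|---|
| 0.3 | 71–74% | 41–45% |
| 0.5 | 99% | 92–95% |

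**The case against.** The strongest reply is that a condensed article is the wrong place to look for multiplicity rules. The SAP is not shown and may hold a hierarchy, an alpha split or a success rule. Several primary outcomes are also legitimate under such a procedure. This stands as far as it goes: the lack of a procedure in the article is no finding. It does not answer the contradiction, because no analysis plan can treat access, knowledge and behavior as primary and as secondary at once. Someone has to choose between the sections.

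The reply also limits the error rates. A reader might infer that every primary outcome is tested at 5% and that any one success makes the trial positive. The article does not say so: 0.05 appears only in the HbA1c calculation, and no success rule is given. Independence is unrealistic too, since controlled blood pressure derives from systolic and diastolic pressure. And because the listed outcomes are directional, the favorable-direction figures are the fairer measure of a falsely positive trial.

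Two further inferences are tempting and unsupported. One is that each aim is tested separately at 3 and 6 months. Data analyses names no visits and mentions only treatment-by-time interaction terms, while the 6-month study period and the 6-month completion assumption point to 6 months. The other is that Objectives demotes lipids and blood pressure. It does not mention them.

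The plural in the sizing paragraph weakens the case for HbA1c as sole primary outcome slightly, but every figure there is for HbA1c.

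**Conclusion.** The point holds as an internal contradiction with a consequence for what the trial may claim. Access and utilization, and knowledge and behavior, are primary in Study outcomes and secondary elsewhere. Lipids and blood pressure are labelled primary but have no sizing. Only HbA1c is both.

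The error rates in step 4 are conditional. They show what would follow if the eight clinical endpoints were each tested at 0.05 without adjustment. On the mildest case examined, favorable errors only at correlation 0.8, the rate is still about three times that of a single test (7.8% against 2.5%). They do not describe a rule that the article states. The power figures in step 5 rest on an SD inferred from the stated sample sizes.

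**What to change.** In Study outcomes, name HbA1c at 6 months as the single primary outcome. This matches the sizing section and its assumption about completion at 6 months. Then reclassify the rest, for two separate reasons:

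- Access and utilization, knowledge and behavior become secondary, to agree with Objectives and CHW intervention.
- Lipids and blood pressure become secondary because only HbA1c is sized. Objectives gives no ground for this either way.

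Make the reference to primary outcomes in Sample size calculations singular.

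This needs no new data or participants, and no sample-size change for multiplicity. The Discussion places final analysis after data collection ends, so the choice can be recorded before group comparisons are seen. The cost is that results on the other endpoints can no longer be headlined as primary. Keeping several primary outcomes is possible only with a stated multiplicity procedure and the same classification in every section, and under Bonferroni it would take much of the power for a 0.3 difference.
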